## Abstract

**Background:**

Cardiovascular diseases (CVD) contribute considerably to mortality and morbidity. Prevention of CVD by lifestyle change and medication is important and needs full attention.

In the Netherlands an integrated programme for cardiovascular risk management (CVRM), based on the Chronic Care Model (CCM), has been introduced in primary care in many regions in recent years, but its effects are unknown.

In the ZWOT-CASE study we will assess the effect of integrated care for CVRM in the region of Zwolle on two major cardiovascular risk factors: systolic blood pressure (SBP) and low-density lipoprotein cholesterol (LDL-cholesterol) in patients with or at high risk of CVD.

**Methods:**

This study is a pragmatic observational study comparing integrated care for CVRM with usual care among patients aged 40–80 years with CVD (*n* = 370) or with a high CVD risk (n = 370) within 26 general practices. After 1 yr follow-up, primary outcomes (SBP and LDL-cholesterol level) are measured. Secondary outcomes include lifestyle habits (smoking, dietary habits, alcohol use, physical activity), risk factor awareness, 10-year risk of cardiovascular morbidity or mortality, health care consumption, patient satisfaction and quality of life.

**Conclusion:**

The ZWOT-CASE study will provide insight in the effects of integrated care for CVRM in general practice in patients with CVD or at high CVD risk.

**Trial registration:**

The ZWOlle Transmural Integrated Care for CArdiovaScular Risk Management Study; ClinicalTrials.gov; Identifier: NCT03428061; date of registration: 09-02-2018; This study has been retrospectively registered.

## Background

Cardiovascular disease (CVD) is still the leading cause of death in the world and the second cause of death in Western societies [1, 2]. Because of the ageing population, the prevalence and associated costs of CVD are expected to increase considerably [3]. Moreover, due to adverse lifestyle factors an increase in the prevalence of obesity and diabetes mellitus has been observed in the past 25 years. In addition, we are dealing with high levels of persistent smoking. These trends partly negate the beneficial effect of improvements in blood pressure and lipid control achieved in the last decades [4]. Therefore, prevention of (re)occurrence of CVD remains crucial.

To prevent CVD, national and international guidelines for cardiovascular risk management (CVRM) provide clinical and organisational recommendations [5–7]. However, implementation of evidence-based guidelines is far from optimal and treatment goals are often not achieved [8–10]. Thus, despite the availability of accurate guidelines, CVRM needs improvement.

In the Netherlands, integrated care programmes were introduced to implement CVRM in general practices in recent years. The integrated CVRM care programme includes a patient-centered focus, use of clinical information systems, execution by practice nurses (PNs) and systematic invitation of patients for a CV risk assessment. The integrated CVRM care programme is based on the Chronic Care Model (CCM) that focuses on informed and activated patients who interact with trained, proactive practice teams [11, 12].

Integrated programmes compose a promising procedure to enhance chronic care and management of cardiovascular risk factors. However, solid evidence on the effect of integrated care programmes for CVRM in primary care on outcomes such as blood pressure, cholesterol levels, smoking status and cardiovascular risk is limited [13–15].

A nurse-coordinated CVD prevention programme (Euro Action) has been shown to improve blood pressure targets [16]. Also, a disease management programme for patients with coronary heart disease (CHD) in primary care led to more adequate treatment of blood pressure and cholesterol compared to usual care and to a better controlled hypertension in high risk patients [17]. Additionally, a tailored implementation of cardiovascular risk management in general practice increases physical activity in cardiovascular patients, but did not affect other cardiovascular risk factors [18]. More recently, a multicomponent cardiovascular prevention programme did not improve the overall risk profile in older adults free from CVD in primary care, compared to usual care [19]. However, the usefulness of these previous studies is restricted by the heterogeneity in study designs, variety in the interventions tested and in the target populations. Most of the previous studies evaluated only a limited number of elements of the disease management programme for CVRM, such as lifestyle treatment or educational interventions. Rarely, effects of an integrated approach programme has been evaluated by analysing clinical parameters before and after implementation of the intervention, but adequate comparisons with control groups are lacking [20].

In the ZWOT-CASE study (ZWOlle inTegrated care for CArdiovaScular risk managEment study) we will investigate the effect of integrated care for CVRM compared to usual care within general practices in the region of Zwolle in the eastern part of the Netherlands. In this paper we describe the design of the study.

## Methods/ design

### Study aim

The primary aim of the ZWOT-CASE study is to investigate whether the execution of an integrated primary care programme for CVRM in general practice leads to a more favourable CV risk profile in patients with known CVD or at high CVD risk as compared to usual care.

### Study design

The ZWOT-CASE study is a prospective pragmatic observational study, performed among 740 patients with known CVD or at high CVD risk in general practice, comparing integrated care for CVRM with usual care. Patients in the usual care group are matched with patients in the intervention group according to age, gender and risk group (high CV risk or CVD). After 1 yr of follow-up outcomes are compared between the intervention group and the usual care group. Primary outcomes are levels of systolic blood pressure and LDL-cholesterol. The study was reviewed by the Isala hospital Review Board and exempted from full assessment under the Medical Research Involving Human Subjects Act on the 16th of June 2016.

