### ZWOT-CASE study population

The ZWOT-CASE study population will consist of a subgroup of 370 patients from the integrated CVRM care group (intervention) and 370 patients in the usual care group. Both groups consist of respectively i) 185 patients with known CVD and ii) 185 patients with a high (> 10%) 10 yr risk of CVD morbidity and mortality based on the Dutch Guideline for CVRM [7, 23, 24].

Inclusion criteria for patients with CVD:
Patients with a history of atherosclerotic CVD defined as documented angina pectoris, myocardial infarction, chronic ischemic heart disease, coronary sclerosis, transient ischaemic attack (TIA), cerebral infarction, intermittent claudication or aneurysm of the abdominal aortaThe CV risk of the patient is managed in primary care, not in the hospital or outpatient clinic by a medical specialistAge between 40 and 80 years

Inclusion criteria for high risk patients:
Use of blood pressure lowering or lipid lowering drugsA 10 -years CV risk > 10%, based on the Dutch guideline for CVRM and i) either 1 strongly cardiovascular risk enhancing factor or 2 mildly cardiovascular risk enhancing factors (see Table 6) or ii) > 1 CV risk factor (current smoking, SBP > 140 mmHg, LDL >  2.5 mmol/L, TC/HDL-ratio > 8, chronic renal impairment (age <  65 years: eGFR < 60 ml/min/1,73 m2; age ≥ 65 years: eGFR < 45 ml/min/1,73 m2, and/or (micro)albuminuria).A 10-year CV risk of > 20% and > 1 CV risk factor (current smoking, SBP > 140 mmHg, LDL >  2.5 mmol/L, TC/HDL-ratio > 8, chronic renal impairment (age <  65 years: eGFR < 60 ml/min/1,73 m2; age ≥ 65 years: eGFR < 45 ml/min/1,73 m2, and/or (micro)albuminuria).The CV risk of the patient is managed in primary care, not in the hospital or outpatient clinic by a medical specialistAge between 40 and 80 years

**Table 6 Tab6:** Risk enhancing factors [7]

	Not risk enhancing	Mildly risk enhancing	Strongly risk enhancing*
First-degree relative with CVD	No	1 family member < 65 years	> 2 family members with CVD < 65 years or 1 < 60 years
Physical activity	≥ 30 min/d, ≥ 5 d/wk	< 30 min/d, ≤ 5 d/wk	Sedentary
Body mass index	BMI < 30 kg/m2	BMI 30–35 kg/m2	BMI > 35 kg/m2
eGFR	< 65 years: > 60 ml/ min/1,73 m2	< 65 years: 30–60 ml/ min/1,73 m2	All ages: < 30 ml/ min/1,73 m2
	≥ 65 years: > 45 ml/ min/1,73 m2	≥ 65 years: 30–45 ml/ min/1,73 m2	

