#### Usual care group

In order to create the same study population as in the intervention group, we identify patients in the usual care group according to the protocol (‘Organized Practice’) as described before, including systematically screening of the practice population based on ICPC-coded diagnoses and ATC-codes, and manually checking of medical records. As the general practices in the usual care group do not start with the integrated care programme for CVRM, patients in the usual care group will not be invited for an intake consultation at baseline. Subsequently, a risk profile based on complete data on age, sex, smoking status, blood pressure and lipid spectrum may be missing. In that case, patients can be included if the 10-yeas risk is at least 10%, based on the data that are available. For example, a 55-year old male patient with a missing smoking status and missing total cholesterol/ HDL- cholesterol ratio can be classified as having a CV risk > 10% based on a known systolic blood pressure of 160 mmHg.

Patients in the usual care group are matched to patients in the intervention group. Therefore, the patient in the usual care group will only be invited for the study after the patient in the intervention group agreed to participate. Patients in the usual care group will be invited by letter and subsequently by telephone. If this patient does not agree with participation in the study, the second matched patient from the usual care group will receive an invitation. If the second matched patient also does not agree with participation, we will randomly invite one of the remaining patients from the usual care group who were not invited for the study.

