#### Matching

Patients in the usual care group are consecutively matched with the intervention group according to age (per 5 years age categories), gender and risk group (high CV risk or CVD) at the beginning of the study. Each patient in the intervention group is matched to 2 patients in the usual care group. These patients in the usual care group are randomly selected from the eligible population in practices delivering usual care.

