### Outcomes and data collection

An overview of the outcomes of the ZWOT-CASE study is shown in Table 7. The primary outcome is systolic blood pressure and LDL-cholesterol. Patients fill out a questionnaire prior to the endpoint-visit including physical activity (squash questionnaire), quality of life (EQ-5D and SF-12), employment (iPCQ), patient satisfaction regarding the provided care (Patient Reported Experience Measure (PREM)), self-management (Patient Activity Measure (PAM)), and anxiety and depression (Hospital Anxiety and Depression Scale (HADS)). Besides, social status, education (UCC-1 questionnaire) [25], food habits, and CV risk perception are measured by a questionnaire.

**Table 7 Tab7:** Primary and secondary outcomes

Primary endpoints	
1. Systolic blood pressure	
2. LDL-cholesterol	
Secondary endpoints	
1. 10-years cardiovascular morbidity or mortality risk (percentage) (Risk chart Dutch guideline or SMART)	
2. Smoking status	
3. Body mass index (BMI)	
4. Lifestyle (modification) (smoking cessation, healthy food habits, physical activity, motivation for modification and awareness of received advices with respect to weight, food habits and physical activity in the past year)	
5. Awareness of CVD and cardiovascular risk factors	
6. Use of adequate medication (blood pressure lowering drugs, anticoagulants and lipid lowering drugs)	
7. Morbidity (newly developed CVD)	
8. Developed comorbidity (CVD, diabetes mellitus, COPD, heart failure, atrial fibrillation)	
9. Mortality	
10. Primary treating practitioner (GP or medical specialist)	
11. Health care consumption in the past year	
12. Self-management in the past year (patient knowledge, skills, and confidence in managing one’s health and healthcare) (Patient Activity Measure (PAM))	
13. Self-measurements of blood pressure in the past year	
14. Patient satisfaction regarding the provided care in the past year Patient Reported Experience Measure (PREM)	
15. Quality of life (EQ-5D and SF-12)	
16. Anxiety and depression (Hospital Anxiety and Depression Scale (HADS)	
17. Cost-efficiency (iPCQ)	

* HIS = general practice information system

Further, a blood sample is taken for measurement of lipids (total cholesterol, HDL-cholesterol, TC/HDL-cholesterol ratio, LDL-cholesterol, triglycerides), renal function (creatinine, MDRD), glucose and for patients with CVD hs-CRP.

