The endpoint visit consists of the same components as the intake consultation in the integrated programme for CVRM as described before. Data collected during the endpoint visit will be registered in the electronic medical record.

An up-to-date 10-years cardiovascular morbidity or mortality risk will be estimated according to the algorithm of the Dutch national guideline for CVRM. This algorithm is based on the SCORE-function, adapted to the Dutch population and converted from a mortality risk to morbidity and mortality risk (based on the MORGEN-cohort and the Rotterdam Study-cohort) [26–29]. The risk chart takes into account age, sex, smoking status, systolic blood pressure and total cholesterol-HDL cholesterol ratio [23, 24]. For patients taking blood pressure or lipid lowering drugs, the actual SBP and cholesterol levels during treatment are used. For patients with CVD the SMART-function will be used to calculate the CV risk [30]. This function is based on age, sex, smoking status, systolic blood pressure, history of diabetes mellitus, ischemic heart disease, cerebrovascular disease, aortic aneurysm, peripheral arterial disease, time since first diagnosis of CVD, HDL-cholesterol, total cholesterol, renal function (eGFR), and high-sensitivity CRP.

Furthermore, baseline data and data concerning health care use in the past year and in the period prior to the study will be collected by scrutinizing the electronic medical files.

Finally, GPs will be asked to complete a survey about the CVRM care, including questions on the practice setting (rural/urban, solo/group), organization of their practice, availability of trained PNs, CVRM programme and possibilities to refer for lifestyle treatment (social map).

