### Statistical analyses

The aim of the main analysis is to compare the SBP and LDL-cholesterol levels after 1 yr of follow-up between patients in the intervention group receiving integrated care for CVRM and the patients in the usual care group receiving usual CVRM care. For the main analysis we will use linear regression. For secondary outcomes, linear regression will be used for continuous outcomes, logistic regression for dichotomous outcomes and multinomial logistic regression for categorical outcomes. All analyses will be corrected for clustering.

Given that patients of clusters of patients are not randomly allocated to the intervention or usual care group, we anticipate that differences in baseline risk might be present between both groups. Hence, we will adjust the analyses for these confounders, including patient characteristics and practice characteristics. To do such adjusted analysis we a priori define the following baseline covariates which are well-known to be related to the outcomes: i) patient characteristics, including relevant medication use, such as blood pressure lowering drugs [32], anticoagulants [33] and lipid lowering drugs [34], relevant comorbidity, including COPD [35], heart failure [36, 37], atrial fibrillation [38], renal failure [39], ii) practice characteristics, such as involved disciplines in CVRM care (including number of PNs) [31], number of patients, and number of GPs. Results will be reported both without (i.e. crude results) and after correction for confounders. Confounders are defined a priori and not selected based on statistical significance.

Furthermore, we will examine whether the effect of the integrated care for CVRM is modified by differences in the following practice characteristics: practice organization (solo/duo/group), availability of CVRM protocol and existence of other disease management programmes (COPD, DM). This will be done by adding interaction effects.

All analyses are applicable to patient data matched on age and gender.

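### In patients with CVD, the SMART 10-year risk is built partly from CVD location and time since first diagnosis, but neither is matched on nor named as a covariate

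*Protocol article*

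**What the plan says.** Study design states that usual-care patients are "matched with patients in the intervention group according to age, gender and risk group (high CV risk or CVD". The Matching section gives the detail: "according to age (per 5 years age categories), gender and risk group (high CV risk or CVD) at the beginning of the study". If both matched controls decline, the section on the usual care group says "we will randomly invite one of the remaining patients from the usual care group who were not invited for the study", with no matching factor stated for that replacement.

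Each arm includes "185 patients with known CVD". The definition of CVD is broad. It begins "Patients with a history of atherosclerotic CVD defined as documented angina pectoris, myocardial infarction, chronic ischemic heart disease, coronary sclerosis" and goes on to cerebrovascular disease, claudication and abdominal aneurysm (ZWOT-CASE study population).

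The first secondary endpoint in Table 7 is "10-years cardiovascular morbidity or mortality risk (percentage) (Risk chart Dutch guideline or SMART". Outcomes and data collection assigns the SMART function to patients with CVD. Among its inputs are "history of diabetes mellitus, ischemic heart disease, cerebrovascular disease, aortic aneurysm, peripheral arterial disease, time since first diagnosis of CVD".

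Statistical analyses sets out covariates chosen in advance: medication use, "relevant comorbidity, including COPD [35], heart failure [36, 37], atrial fibrillation [38], renal failure [39", and practice characteristics. CVD location, time since first CVD diagnosis and baseline SMART score are not named. The same section expects the arms to differ in baseline risk and promises both crude and adjusted results.

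**The concern.** The disease history that a patient brings to t = 0 is not something the programme can alter, yet it forms part of the SMART score by construction. If one arm has more patients with, say, a second vascular site or a longer disease history, its mean SMART risk is higher even when the programme does nothing. Neither the matching nor the listed covariates would remove that difference, so it would be read as benefit or harm of the programme. The direction cannot be predicted.

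The second cost is precision. Variation in risk that comes from fixed history stays in the residual, although the trial must record that history to compute the score at all.

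**Working it through.** **Step 1. SMART inputs set against the controls in the plan**

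| SMART input | How the plan controls it |
|---|---|
| Age, sex | Matched (5-year bands, gender), apart from replacement controls |
| Diabetes | Excluded |
| Kidney function | Partly, through the renal-failure covariate |
| CVD location (four terms) | Not matched, not named as covariate |
| Time since first CVD diagnosis | Not matched, not named as covariate |
| Smoking, SBP, cholesterol, hs-CRP | Can move during follow-up, so part of what is being compared |

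Of the inputs fixed before t = 0, CVD location and duration are the ones left without any stated control.

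**Step 2. Inputs for an illustration of size**

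The plan gives no figure for this endpoint, so there is nothing to reproduce.

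- From the documents: 185 patients with CVD per arm; 17 and 9 practices; ICC 0.05; alpha 0.05 (taken as two-sided). The ICC is the one given in Sample size calculation and is assumed to apply here too.
- Assumed: SD of 10-year risk 12 points (range 10 to 15); a CVD type present in 30% of patients; a 10 to 15 point gap in predicted risk between types; a systematic 10-point difference between arms in the share with that type.

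**Step 3. Standard error of the unadjusted comparison**

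Design effect = 1 + (m - 1) x ICC, where m is the number of CVD patients per practice.

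- Integrated care: m = 185/17 = 10.9, so 1 + 9.88 x 0.05 = 1.49
- Usual care: m = 185/9 = 20.6, so 1 + 19.56 x 0.05 = 1.98
- SE = 12 x sqrt((1.49 + 1.98)/185) = 1.64 points

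**Step 4. Bias and false-positive rate when the programme has no effect**

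Bias = difference in mix x gap in risk: 0.10 x 10 = 1.0 point, and 0.10 x 15 = 1.5 points.

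Rejection rate = 1 - Phi(1.96 - bias/SE) + Phi(-1.96 - bias/SE):

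- Bias 1.0: bias/SE = 0.61, rejection 9.3%
- Bias 1.5: bias/SE = 0.91, rejection 14.9%
- With SD from 10 to 15, the range is 7.8% to 19.5%

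**Step 5. Precision gained by adjusting for CVD type**

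Variance due to type = p(1 - p) x gap squared = 0.21 x 100 = 21 up to 0.21 x 225 = 47. Against a total of 12 squared = 144, R2 is 0.15 to 0.33. The SE is multiplied by about sqrt(1 - R2) = 0.92 to 0.82, a reduction of about 8 to 18%. Disease duration would add to this by an amount the documents do not allow to be estimated.

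**Step 6. Chance imbalance, for comparison**

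At 30% prevalence the SD of the between-arm difference in share is sqrt(0.21 x (1.49 + 1.98)/185) = 0.063, so the 95% range is about plus or minus 12 percentage points. This is sampling variation, which a clustered standard error already reflects. It shows that a 10-point difference would not be remarkable in size, but it is not itself bias.

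**The case against.** **The reach is narrow.** SMART is one version of one of 17 secondary endpoints, and it applies to half the patients. This stands. A reader might infer that SBP and LDL-cholesterol are compromised in the same way. The documents do not support that: neither is computed from disease history. Case mix could relate to them indirectly, but nothing in the article allows that to be sized.

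**The arms may well be alike.** Usual-care patients are identified by the same coded screening and record check, under the same CVD definition and the same requirement of primary-care management. All practices share one care group and one regional hospital. This stands too, and it rules out saying that the arms have no reason to resemble each other. It is also tempting to argue that easier specialist consultation gave integrated-care practices a different CVD population. The article describes online consultation, not transfer of patients, and intake visits were offered within a year of the programme opening, so that mechanism is speculation. What remains is that common screening does not balance CVD mix or duration between self-selected practices, and the authors themselves expect baseline differences.

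**The covariate list is open and the article is condensed.** The list is worded as examples. But the article does not defer the covariates to another document. It names them and says they are fixed in advance, and that wording does not commit the analysts to the two variables the endpoint is built from.

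**Disease location is not strictly fixed.** A new vascular event during follow-up changes the location terms. This is correct, and it is why the covariates should carry their t = 0 values: an event during follow-up then stays in the outcome.

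**Conclusion.** The point holds for the SMART risk in patients with CVD. The stated matching and covariates leave two direct, pre-existing components of that endpoint uncontrolled in a non-randomised comparison. This follows from the text and needs no numerical assumption.

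The size does need assumptions. The bias of 1.0 to 1.5 points and the false-positive rate of about 9 to 15% hold only if a 10-point difference in CVD mix is systematic, and the article gives no evidence that it is. The SD and the risk gap between types are also assumed, because the article gives no SMART coefficients or distribution. On the same inputs, adjusting for CVD type narrows the standard error by about 8 to 18%. A reader might expect far more: if fixed history explained 70% of the variance, the reduction would be 1 - sqrt(0.3) = 45%. The inputs for CVD type do not reach that, and nothing in the documents shows that duration would supply the rest.

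This is a worthwhile correction to one secondary analysis. It is no threat to the primary comparison.

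**What to change.** In Statistical analyses, add to the a priori covariates, for the SMART endpoint in patients with CVD:

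- CVD location (coronary, cerebrovascular, peripheral, aneurysm; more than one allowed), and
- years since first CVD diagnosis,

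both dated at t = 0. State that this adjusted model is the main reported effect for the SMART endpoint, with the crude result alongside. The matching can stay as it is.

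The cost is a sentence or two and about five coefficients (four location terms and one for duration) in a model for 370 patients with CVD (2 x 185). No new data are needed, since SMART cannot be computed without these variables and review of the medical files is already planned. Adjustment removes the bias to the extent that the model form is right.
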